### Semi-structured focus group discussion

A qualitative component was incorporated in this study to obtain a deeper understanding of the perceived effectiveness of the structured physiotherapy intervention. A post-intervention focus group discussion (FGD) will be conducted among parents and caregivers whose children completed the 12-week programme. The FGD aimed to explore caregivers’ experiences, perceived changes in their child’s motor skills, physical activity levels, behaviour, and overall QoL following the intervention. Key discussion prompts included perceptions of motor skills levels, noticeable differences between usual care and the structured physiotherapy sessions, the acceptability and practicality of the intervention, and the perceived value of continuing the programme. The semi-structured FGD interview protocol including main questions and probing cues is presented in Table S1. The FGD will be conducted a week after completion of all post-intervention assessments and will last approximately 45–60 min. This FGD provided contextual insights that complemented quantitative findings and informed the interpretation of the intervention’s real-world relevance and feasibility.

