### Sample size calculation

The sample size for this study was calculated using G*Power software version 3.1.9.4, employing an F-test for repeated-measures analysis of variance (ANOVA) with a within–between interaction [20]. The calculation was based on an alpha level of 0.05, a statistical power of 80 % (1–β = 0.80) and an effect size (f) of 0.12. This effect size was derived from the previous study [21] which investigated motor skill outcomes using the BOT-2 which is the primary outcome measure in the present study. The Cohen’s d reported in the previous study [21] was converted to Cohen’s f using the online tool provided by https://www.escal.site/. Based on these parameters, the minimum required sample size was calculated to be 58 participants. Additionally, accounting for an anticipated dropout rate of 10 % the required sample size is 64 participants, with 32 participants allocated to each group.

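### The focus group admits only caregivers of children who completed the programme, so its themes on acceptability, practicality and feasibility lean towards a favourable picture

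*Protocol article*

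**What the plan says.** All of the following is in the Protocol article.

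- **Who takes part** (Semi-structured focus group discussion): "A post-intervention focus group discussion (FGD) will be conducted among parents and caregivers whose children completed the 12-week programme".
- **When** (same section): "The FGD will be conducted a week after completion of all post-intervention assessments".
- **What they are asked** (same section): the prompts cover motor skills, differences from usual care, and "the acceptability and practicality of the intervention, and the perceived value of continuing the programme". The section gives the main purpose as understanding how effective the intervention is perceived to be.
- **How the output is used** (same section): the discussion is said to have "informed the interpretation of the intervention’s real-world relevance and feasibility".
- **Expected loss** (Sample size calculation): "accounting for an anticipated dropout rate of 10 % the required sample size is 64 participants", "with 32 participants allocated to each group".

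The Trial design section and the specifications table describe the qualitative sample more broadly, as children and their parents or caregivers. Neither says that families who stopped early are included. The Strengths and limitations section does not mention the completer restriction.

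**The concern.** To enter the focus group, a family must have stayed to the end. One thing the group is then asked is whether the programme is acceptable, practical and worth continuing. A family that found it unworkable is more likely to have left, and so less likely to be asked.

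What is at stake is one part of the qualitative conclusions. If the report says that caregivers found the programme acceptable and feasible, a reader may take this to describe families offered the programme. It would describe only families who finished it. For judging real-world use, the views of those who stopped are among the more informative, and under this rule the focus group cannot hear them first-hand.

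**Working it through.** **1. The plan's own figure.** The only stated number that bears on how many families are excluded is the dropout allowance. The section on sample size says "the minimum required sample size was calculated to be 58 participants" before that allowance.

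- Adding 10 %: 58 × 1.10 = 63.8, rounded up to 64, or 32 per group. This reproduces the stated total.
- Dividing by the retained fraction: 58 / 0.90 = 64.4, rounded up to 65.

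The difference is one participant and has no bearing here. Nor does the point depend on how the 58 was obtained.

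**2. How many families the rule could exclude.** Inputs: 32 allocated to the intervention and 10 % dropout. The 10 % is given for the whole sample; applying it to the intervention group alone is an assumption.

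- Expected non-completers: 0.10 × 32 = 3.2, so about 3 families.
- Chance of at least one, if families drop out independently: 1 − (1 − 0.10)^32 = 0.966.
- Range for other dropout rates, which are assumed:

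| Dropout | Expected of 32 | Chance of at least one |
|---|---|---|
| 5 % | 1.6 | 0.806 |
| 10 % (planned) | 3.2 | 0.966 |
| 20 % | 6.4 | 0.999 |

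The plan therefore expects non-completers to exist. The article sets no number of sessions that counts as having completed. If the word means remaining to week 12, partial attenders are already eligible. If it means attending most or all of the 24 sessions, more families are excluded than the dropout rate suggests.

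**3. Which conclusions are affected.** The section can be separated by topic.

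| Topic | Does restriction to completers matter? |
|---|---|
| Perceived change in motor skills, activity, behaviour and quality of life after the programme | Little. Caregivers who saw all of it are a reasonable sample for this. |
| Acceptability, practicality, value of continuing | Yes. Staying to the end is plausibly related to these. |
| Real-world relevance and feasibility, as an interpretation | Yes, so far as it draws on the row above. |

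**4. Direction.** The tilt is favourable if non-completers view the programme less favourably than completers, and absent if the two groups think alike. The article does not state the relation, but its content makes it plausible. The Intervention section asks for two one-hour sessions a week for 12 weeks, with parents encouraged to join in and continue practice at home. The Safety section foresees that a child's motivation may fall.

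**5. Is it offset elsewhere?** The Data analysis section applies intention to treat, which keeps non-completers in the quantitative comparison. It does not bring them into the focus group. The article describes no other route by which their views on acceptability would reach the qualitative findings.

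**The case against.** The strongest reply is that the focus group is mainly about perceived effectiveness and change. Acceptability and practicality are one prompt among several, and for perceived change after 12 weeks, families who saw the whole programme are a defensible purposive sample. This stands, and it confines the point to the acceptability, practicality and feasibility themes.

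Three stronger readings are tempting, and the document does not support them.

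- **That the discussion can only come out favourable.** Caregivers of completers can still report burden, scheduling difficulty or little benefit, and the prompts invite this. Children may decline activities without leaving, so families with poorly engaged children can remain eligible. The sample is tilted, not one-sided.
- **That acceptability would read 29/29 (100 %) instead of 29/32 (91 %).** Those figures require every completer to approve, every non-completer to disapprove, and all 29 completing families to be heard. The article says none of this. It gives no focus group size, and its thematic analysis yields no such proportion.
- **That the reasons for stopping are lost altogether.** The article condenses a fuller protocol and commits to CONSORT and SPIRIT. Its silence about a withdrawal record does not show that there is none. What can be said is that the focus group, as defined, will not supply those reasons first-hand.

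It may also be said that the full protocol and the discussion guide in Table S1 are not shown. However, the article describes Table S1 as holding questions and probing cues, and it states the rule on who takes part outright. The point concerns that stated rule, not a missing detail. Finally, some families will leave for reasons unrelated to the programme. That weakens the tilt but does not remove it.

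**Conclusion.** The point holds in a limited form. The article restricts the focus group to caregivers of completers and then uses it for acceptability, practicality, the value of continuing, and real-world relevance and feasibility. Themes on those matters lean favourable; themes on perceived change after the full programme do not share the problem.

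The size is best given as a count: about 3 of 32 intervention families outside the group at the planned 10 % dropout, with the number depending on how completion is defined. No percentage bias can be stated. The direction rests on one assumption, that completion is related to how acceptable a family finds the programme. This is plausible, but the article does not say it.

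The primary BOT-2 comparison and the other quantitative analyses are untouched. This is a minor improvement, worth making because it is cheap.

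**What to change.** In the Semi-structured focus group discussion section, change the sampling rule so that caregivers of all children allocated to the intervention are invited, including those whose children stopped early or attended only part. Use the same guide for the acceptability and practicality prompts. A short individual conversation can be offered to those who do not wish to join a group. Report how many non-completers were invited and how many took part. State what counts as having completed, so that the two sets of families can be told apart.

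If the rule is kept, limit the acceptability and feasibility conclusions to families who completed, and add the restriction to Strengths and limitations.

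The cost is about three extra invitations at the planned dropout, some of which will be declined, and possibly a minor amendment. According to the Protocol validation section, intervention delivery is under way but outcome assessments have not begun. The focus group follows those assessments, so on the article's account there is still time for the change.

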### Data analysis

Data will be analysed using IBM SPSS Statistics Version 28. Descriptive statistics will summarise participant characteristics, and baseline comparability between groups will be evaluated using independent *t*-tests or chi-square tests. All analyses will follow the intention-to-treat (ITT) principle, with missing data handled using last observation carried forward (LOCF) and will be supported by sensitivity analyses using multiple imputation. A 2 × 2 mixed-design ANOVA (group × time) will examine within and between-group differences across the intervention period. Significant interactions will be examined using Bonferroni-adjusted post hoc tests. Effect sizes will accompany all significance tests, including Cohen’s d for mean differences and partial eta squared (η²p) for ANOVA effects, with 95 % confidence intervals reported. Statistical significance will be set at *p* < 0.05. Qualitative data will be analysed using thematic analysis following Braun and Clarke’s six-phase protocol [35].

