## Abstract

Children with Autism Spectrum Disorder (ASD) frequently experience psychomotor impairments, limited participation in physical activities, and reduced quality of life (QoL). Exercise shows promising benefits, but physiotherapy approaches in ASD are underreported, with limited evidence supporting a structured framework that systematically targets motor and functional outcomes. This study protocol describes a single-blinded randomised controlled trial evaluating the effectiveness of a structured physiotherapy intervention on motor skills, physical activity levels, and behavioural and QoL among children with mild to moderate ASD. This trial will include 64 children aged 6–10 years with ASD. Participants will be randomly assigned to an intervention group or a control group. Both groups will receive usual care therapy, equated between groups. The intervention group will also receive structured physiotherapy twice weekly for 12 weeks, each session lasting 60 min. The intervention integrates coordination, balance, strength, and endurance training. Outcome assessments will be conducted at baseline and post-intervention using validated instruments: GARS-3, BOT-2, GLTEQ, CBCL and PedsQL. Data analysis will follow the intention-to-treat principle and will examine between-group and within-group changes across all outcome measures. Qualitative data will be analysed using thematic analysis to characterise themes reflecting participants' engagement and parents' and caregivers' perspectives on the intervention.

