### Participant screening, recruitment and randomisation

All children with ASD will be screened and recruited from the sampling frame of participating centres, using simple random sampling. The screening, recruitment, and randomisation procedures will be conducted by an independent researcher who is not involved in data collection or outcome assessment. Screening assessments of GARS-3 and BOT-2 Short Form will be conducted before randomisation to determine eligibility. As these assessments will be administered immediately before group allocation and under the same standardised conditions required for baseline measurement, the screening scores will be used as baseline data to minimise participant burden and avoid unnecessary repetition of measures. Eligible participants and their caregivers will receive clear, comprehensive information about the study through written materials and verbal explanations. This will include the study objectives, procedures, potential risks and benefits, and the anticipated time required for participation. After confirming their understanding, parents or legal guardians will be asked to provide written informed consent. Assent will also be obtained from the participating children in accordance with ethical standards for research involving minors. Only children classified as having mild to moderate ASD according to the GARS-3 will be invited to attend a motor skills assessment using BOT-2 Short Form. If a selected participant declines, the next name on the list will be contacted to achieve the desired recruitment target. Screening will take place over a two-week period, during which eligibility will be confirmed. Following confirmation of eligibility, participants will be randomised into either the intervention or control group using a computer-generated randomisation sequence (randomization.com). To reduce potential confounding, stratified randomisation will be applied by age group (6–8 years vs. 9–10 years) and ASD severity (mild vs. moderate, based on GARS-3). This approach will balance participant characteristics across study arms and ensure that outcomes reflect the intervention's effect independent of these variables. Allocation concealment will be maintained to prevent selection bias. Children who are successfully randomised will then be scheduled for baseline parent proxy assessments, conducted before the initiation of the intervention. GARS-3 and BOT-2 Short Form scores obtained during screening will serve as baseline values, while the GLTEQ, CBCL, and PedsQL will be administered as parent-proxy assessments following randomisation but before the intervention begins. All five outcome measures will be re-administered at post-intervention. This sequence ensures that group allocation is unbiased and that baseline data reflect participants’ pre-intervention status. A SPIRIT schedule of enrolment, interventions, and assessments is shown in Fig. 1.

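### With one post-baseline assessment, LOCF as the main method sets change to zero for every child without a post-intervention score, which generally biases the group × time estimate in a direction that is not fixed

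*Protocol article*

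**What the plan says.** The Data analysis section of the protocol article states that "All analyses will follow the intention-to-treat (ITT) principle". It then specifies how incomplete outcomes enter those analyses: "with missing data handled using last observation carried forward (LOCF) and will be supported by sensitivity analyses using multiple imputation". LOCF is thus the main method and multiple imputation the supporting one. The same section fixes the model: "A 2 × 2 mixed-design ANOVA (group × time) will examine within and between-group differences across the intervention period".

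The measurement schedule has two occasions. The Abstract says "Outcome assessments will be conducted at baseline and post-intervention using validated instruments". The section on screening, recruitment and randomisation says "All five outcome measures will be re-administered at post-intervention", and for the autism rating and the primary motor outcome adds that "GARS-3 and BOT-2 Short Form scores obtained during screening will serve as baseline values". No interim outcome measurement is described.

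The Sample size calculation section uses "an alpha level of 0.05, a statistical power of 80 % (1–β = 0.80) and an effect size (f) of 0.12", reports that "the minimum required sample size was calculated to be 58 participants", and raises this to 64 (32 per arm) for an anticipated 10% dropout.

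**The concern.** With two occasions, the only earlier value available is the baseline; for the BOT-2 Short Form, that is the screening score. A missing post-intervention score is replaced by that value, so the child's change is exactly zero and the analysis treats it as observed. In a 2 × 2 design the group × time interaction is the between-arm difference in mean change, so these zeros enter the effect estimate directly.

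Nothing in the protocol argues that children lost to follow-up would not have changed, and two features point the other way. The trial is powered on the intervention producing change. Also, children must show motor difficulties on the test whose screening score then serves as baseline, so some upward regression on retest is possible in either arm.

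At stake are the headline estimate, its interval and its p-value for the primary outcome in a trial of 64 children.

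**Working it through.** **Inputs from the protocol.** f = 0.12, alpha 0.05, power 0.80, 58 evaluable children, 10% dropout, 64 randomised (32 per arm), two measurement occasions.

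**Inputs assumed.** The correlation between baseline and post-intervention scores (rho), the mean change in controls (c), and the split of dropout between arms. The protocol gives none of these.

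**Step 1: reproduce the plan's figure.** For the within–between interaction with two groups and m = 2 occasions, the noncentrality is λ = f² × N × m / (1 − rho), with 1 and N − 2 degrees of freedom. At rho = 0.80 and N = 58, λ = 0.0144 × 58 × 2 / 0.20 = 8.35 and power is 0.811, so 58 is reproduced. Other values of rho give different sizes (0.7 gives 84; 0.5 gives 140), so rho = 0.8 is used below. For dropout, 58 × 1.10 = 63.8, or 64; dividing by 0.90 gives 65. The one-child difference does not matter here.

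**Step 2: put the effect on the SD scale.** In a 2 × 2 design f = Δ / (4 SD), so Δ = 4 × 0.12 = 0.48 SD for the difference in change.

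**Step 3: expected LOCF estimate.** Let dI and dC be the proportions without a post-intervention score, unrelated to outcome. Then

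E = (1 − dI)(c + Δ) − (1 − dC)c, so bias = −dI(c + Δ) + dC·c.

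| dI / dC | c (SD) | Calculation | E (SD) | E / 0.48 |
|---|---|---|---|---|
| 10% / 10% | any | 0.90 × 0.48 | 0.432 | 0.90 |
| 15% / 5% | 0 | 0.85 × 0.48 | 0.408 | 0.85 |
| 15% / 5% | 0.24 | 0.85 × 0.72 − 0.95 × 0.24 | 0.384 | 0.80 |
| 5% / 15% | 0.24 | 0.95 × 0.72 − 0.85 × 0.24 | 0.480 | 1.00 |
| 5% / 15% | 0.48 | 0.95 × 0.96 − 0.85 × 0.48 | 0.504 | 1.05 |

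Every row keeps overall loss at the planned 10%. The estimate can be too small, right by cancellation, or too large.

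**Step 4: no true effect (Δ = 0).** Bias = (dC − dI) × c. It is zero whenever loss is equal. With c = 0.24 and 5% / 15% it is 0.10 × 0.24 = +0.024 SD; with c = 0.48 it is +0.048 SD.

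**Step 5: simulated rejection rates** (32 per arm, rho = 0.8, SD of change √(2 × 0.2) = 0.632, loss unrelated to outcome).

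| Scenario | LOCF | Observed data |
|---|---|---|
| Δ = 0.48, 10% / 10%, c = 0 | 80% | 80–81% |
| Δ = 0.48, 10% / 10%, c = 0.24 | 78% | 80% |
| Δ = 0.48, 15% / 5%, c = 0 | 75% | 81% |
| Δ = 0.48, 15% / 5%, c = 0.24 | 68% | 81% |
| Δ = 0, 10% / 10%, c = 0.24 | 5.1% | 5.2% |
| Δ = 0, 5% / 15%, c = 0.24 | 5.6% | 5.1% |
| Δ = 0, 5% / 15%, c = 0.48 | 6.1% | 4.9% |

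**The case against.** The case for leaving the plan alone has four parts.

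- **The planned case is mild.** With 10% loss in each arm, about 6 of 64 children, the estimate falls by a tenth, power barely moves and the type I error rate is unaffected. This stands, and it sets the severity.
- **The worse cases rest on assumptions.** The protocol gives no dropout by arm and no control change. The primary outcome is scored against age norms, so maturation alone should add little in controls. Twenty-four sessions could plausibly cause more loss in the intervention arm, but no passage says so. This also stands: the unequal splits illustrate the range and do not forecast it.
- **Multiple imputation is already planned.** It would show a discrepancy. It would not change the headline result, which would still be the LOCF one.
- **Imputation has its own assumption.** Under missing at random, a child who left the programme is credited with the change predicted from comparable children who were assessed. That differs from zero change, and is not plainly weaker for children who stopped attending.

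A reader might infer that the effect estimate is certain to be biased, or that LOCF will create a false benefit. The documents support neither. Only children lacking the post-intervention score are affected; a child who stops sessions but is still assessed is not imputed. Bias disappears if such children on average do not change, or if the errors cancel. With no true effect, a false benefit needs controls to improve and loss to be greater in the control arm (or the mirror image: both arms worsening with greater loss in the intervention arm). An error rate of about 7% appears only with an assumed 0.4 SD control gain and 20% control loss against 5%.

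**Conclusion.** The concern holds in conditional form. The protocol itself fixes LOCF as the main method on a two-occasion schedule, so this is not a detail left to an unseen analysis plan. The bias has no fixed sign, so LOCF cannot be defended as a cautious choice.

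The size is modest at the planned loss: 0.43 SD instead of 0.48 SD. It is larger if the same total loss falls mainly on the intervention arm: 0.41 SD, or about 0.385 SD if controls also improve by 0.24 SD. These figures rest on rho = 0.8, on the assumed splits and control change, and on loss unrelated to outcome. The point should be fixed, but it does not undermine the trial.

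**What to change.** Make the primary analysis either the multiple imputation already planned or a likelihood-based or baseline-adjusted model. Include group, baseline score and the two stratification factors (age group and autism severity). Drop LOCF, or keep it as a labelled sensitivity analysis.

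The cost is an amendment to the protocol text and a primary result that rests on a missing-at-random assumption, which should be stated. No additional children, visits or measurements are needed. The Protocol validation section reports that recruitment and delivery are under way but that outcome assessments had not begun, which indicates that the change can be made before any post-intervention result is known.

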### Inclusion and exclusion criteria

Participants will be selected based on specific inclusion and exclusion criteria to ensure the sample is relevant. The inclusion criteria are as follows: (i) aged between 6 and 10 years old, (ii) have a confirmed diagnosis of ASD according to the DSM-5-TR, (iii) classified as having mild to moderate severity based on the GARS-3 autism index (55–100; level 1–2). (iv) demonstrate motor difficulties on the BOT-2 Short Form (iv) able to follow simple verbal instructions (v) have written informed consent provided by a parent or legal guardian. The exclusion criteria include (i) having sensory or physical impairments that would limit their ability to participate in the intervention, (ii) other neurological or developmental conditions such as epilepsy or cerebral palsy, or if they have physical disabilities arising from head injury or other acquired conditions, (iii) having co-occurring diagnosis such as Attention Deficit Hyperactivity Disorder and Down Syndrome, (iv) currently involved in another clinical trial or intensive motor programme, and (v) unstable medical conditions or recent changes in medical treatment.

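### The group × time ANOVA is a valid but less efficient primary test than a baseline-adjusted comparison, and the planned within-group changes cannot show an effect

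*Protocol article*

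**What the plan says.** The Data analysis section plans a 2 × 2 mixed ANOVA, group by time, which "will examine within and between-group differences across the intervention period". Bonferroni-adjusted post hoc tests follow when the interaction is significant. The Abstract likewise says that the analysis "will examine between-group and within-group changes across all outcome measures". No baseline-adjusted model is named, and the two randomisation strata (age group and GARS-3 severity) do not appear in the model.

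The sample size rests on the same test, "employing an F-test for repeated-measures analysis of variance (ANOVA) with a within–between interaction", with "an alpha level of 0.05", 80% power and "an effect size (f) of 0.12". This gives 58 children, or 64 after an allowance for dropout. The pre-post correlation is not stated.

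Two other statements bear on the point. To enter, a child must "demonstrate motor difficulties on the BOT-2 Short Form"; no cut-off is given. And the section on screening, recruitment and randomisation says that GARS-3 and BOT-2 Short Form "scores obtained during screening will serve as baseline values". The GLTEQ, CBCL and PedsQL baselines are reported by parents after randomisation and before the intervention starts.

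**The concern.** There are two separate issues.

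- **Efficiency.** A change score subtracts the whole baseline value whatever the correlation between the two measurements. A regression on baseline subtracts only the part that predicts the outcome. In a trial of 64 children, power on the primary outcome is given up although the covariate is already collected.
- **Interpretation.** The plan presents within-group change as a result alongside the between-group comparison. When children are chosen for low scores and the selecting score is kept as baseline, their mean is expected to rise on retesting without any treatment. A significant rise in the intervention arm could then be read as benefit.

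**Working it through.** **Inputs from the protocol (Sample size calculation):** f = 0.12, alpha 0.05, power 80%, N = 58 before dropout. In a 2 × 2 interaction with equal SDs, f is one quarter of the difference in change, so f = 0.12 means δ = 4 × 0.12 = 0.48 SD.

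**Assumed:** the pre-post correlation ρ, and the BOT-2 entry cut. Neither is given, so ranges are shown.

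**Step 1. Reproduce the stated N.** For the interaction, the noncentrality is λ = f² × N × 2 / (1 − ρ), with 1 and N − 2 degrees of freedom. At ρ = 0.8: λ = 0.0144 × 58 × 2 / 0.2 = 8.35, power 81.1%, and 58 is the smallest even N that reaches 80%. Solving for ρ gives 0.79 to 0.80. At ρ = 0.5 the same formula would need 140 children. The stated N therefore implies ρ of about 0.8.

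**Step 2. Compare with a baseline-adjusted model.** With equal pre and post variances σ², the change score has variance 2(1 − ρ)σ² and the adjusted outcome (1 − ρ²)σ². The ratio is (1 + ρ)/2. For ANCOVA, λ = N δ² / [4(1 − ρ²)], with 1 and N − 3 degrees of freedom. At ρ = 0.8: λ = 58 × 0.2304 / (4 × 0.36) = 9.28, power 84.9%.

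| ρ | variance ratio | power at N = 58, interaction | power at N = 58, ANCOVA |
|---|---|---|---|
| 0.5 | 0.75 | 43.5% | 54.5% |
| 0.6 | 0.80 | 51.9% | 61.2% |
| 0.7 | 0.85 | 64.0% | 71.0% |
| 0.8 | 0.90 | 81.1% | 84.9% |
| 0.9 | 0.95 | 98.0% | 98.5% |

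Simulation at ρ = 0.8 (8,000 runs) gave 80.8% and 83.7%, so the gain there is 3 to 4 points. The number required falls from 58 to 52.

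**Step 3. Regression to the mean and its effect on Step 2.** Let the source-population score be standard normal with retest correlation 0.8, and admit children below a cut c. Write h = φ(c)/Φ(c). With no treatment effect:

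- expected gain in each arm = (1 − ρ)h
- baseline variance among those admitted: v = 1 − ch − h²
- variance of change = (1 − ρ)²v + (1 − ρ²) = 0.04v + 0.36

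The last column gives the chance that an unadjusted 5% pre-post test in one arm of 29 is significant.

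| entry rule (assumed) | gain, population SD | v | ratio ANCOVA/change | within-arm test significant |
|---|---|---|---|---|
| 88% qualify | 0.05 | 0.68 | 0.93 | 7% |
| 80% qualify | 0.07 | 0.58 | 0.94 | 9% |
| cut at the mean | 0.16 | 0.36 | 0.96 | 27% |
| cut at −1 SD | 0.30 | 0.20 | 0.98 | 74% |

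For the last row: h = 1.525, gain = 0.2 × 1.525 = 0.305, ratio = 0.36/0.368 = 0.98. Taking 0.48 in population SDs, power at N = 58 is then 84.2% for the interaction and 84.9% for ANCOVA; with a cut at the mean it is 83.5% and 84.9%.

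**Step 4. Validity of the between-group test.** In simulation with no effect, a −1 SD cut and ρ = 0.8, the interaction rejected in 5.1% of trials and ANCOVA in 5.0%.

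**The case against.** The best defence is that the planned primary test is sound and matches the test used for sizing. This stands. Both arms are selected in the same way, so regression to the mean cancels in the group × time contrast on average. A reader might infer that selection on the BOT-2 biases the primary comparison. It does not: it affects that contrast only through chance baseline differences between arms, which adjustment corrects.

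A second inference is that the plan forfeits a large amount of power, such as 43.5% against 54.5%. Those figures belong to ρ = 0.5, at which the protocol's own formula would need 140 children. The trial would be underpowered with either model, which is a separate sample-size question.

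Nor can the full power gain and the full regression to the mean be claimed together. The 0.90 ratio assumes no selection, in which case there is no regression; a cut strong enough to produce 0.30 SD leaves a ratio of 0.98. The strong cut may also be unrealistic. The Background puts motor impairment of clinical significance at 80–88% of children with ASD; if the entry rule admits a similar share, the regression is only 0.05 to 0.07 SD. These are source-population SDs, so they should not be set directly against the 0.48 SD used for sizing.

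Finally, the post hoc step runs only after a significant interaction, which occurs about 5% of the time with no effect, and it may include a between-group test at post-intervention as well as within-arm tests. It is therefore not the main route to a false claim. What remains is the general promise of within-group results under Data analysis and in the Abstract, which has no such gate.

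**Conclusion.** The point holds as an improvement to a valid analysis. It does not show that the planned test is invalid. The change-score comparison is no more efficient than the baseline-adjusted one, apart from the small cost of estimating one extra coefficient. At the implied correlation of about 0.8 with equal variances, the gain is about 4 points of power (81% to 85%). It falls to about 1 point with a cut at −1 SD and is larger if the true correlation is lower.

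The within-group results are the clearer weakness. An arm's pre-post change mixes any treatment effect with regression to the mean of about 0.05 to 0.30 SD, at an assumed source-population correlation of 0.8. The true size cannot be known without the entry cut. It should not be offered as evidence of effectiveness.

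**What to change.** - Make the primary analysis an ANCOVA of the post-intervention BOT-2 Short Form standard score on group, adjusted for baseline BOT-2 Short Form score, age group and GARS-3 severity. Report the adjusted mean difference with its 95% CI.
- Report within-group change descriptively, without p-values, and drop the post hoc tests of the interaction.
- Use the same model for the secondary outcomes. State that the GLTEQ, CBCL and PedsQL baselines are parent-reported after randomisation, when knowledge of allocation could influence them. Adjustment is cleanest for the BOT-2 Short Form and GARS-3, whose baselines precede randomisation.

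The cost is a change of wording in the analysis plan, with no new data or visits. The Protocol validation section says that outcome assessments had not begun, so on that statement the change could still be specified before outcome data exist.
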